### **Analysis of predictors and moderators**

We will analyse predictors and moderators of response and remission status at 3- and 12-month follow-up using repeated k-fold cross validation with 10 folds and 20 repeats to reduce the risk of model instability (49, 50). We then average model performance over the repeats using area under the receiver operating characteristic curve (AUC) of sensitivity and specificity to

distinguish between responders/remitters and non-responders/non-remitters (51).

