## Remaining evidence gaps that need to be closed

Although multiple research groups have found that therapist-guided ICBT is a promising approach for treating OCD, there are several critical issues that need to be addressed before the implementation of ICBT in a regular health care context can be recommended. **First**, it is unclear if ICBT is non-inferior to gold standard f2f CBT. **Second**, we do not know if our ICBT treatment is equally effective when delivered unguided. **Third**, there are no high-quality cost-effectiveness studies on ICBT for OCD and it is crucial to make a full health economical evaluation of ICBT vs. the gold standard f2f CBT. **Fourth**, the existing studies supporting the efficacy of ICBT in OCD have all relied on self-referred subjects. Self-referred subjects may be less complex, have better insight into their difficulties and be more motivated for treatment and therefore potentially affecting the generalizability of previous findings.(26) **Fifth**, since we do not yet know for whom ICBT is particularly suitable, the identification of reliable predictors and moderators of treatment outcome aid in choosing the right treatment from the start.

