### *Secondary objectives*

2. To investigate if ICBT for OCD can be delivered without therapist support without impairing efficacy.
3. To determine if ICBT, compared to f2f CBT, is a cost-effective treatment for OCD.
4. To examine if there is a difference in treatment outcome between self-referred and clinically referred patients.
5. To explore predictors and moderators of treatment outcome as a first step towards personalized treatment selection.

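### The moderator part of objective 5 cannot be answered by its only stated criterion: cross-validated AUC for response status measures prediction of outcome, not a difference in treatment effect

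*Combined protocol and SAP*

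**What the plan says.** Objective 5 (Secondary objectives) is "To explore predictors and moderators of treatment outcome as a first step towards personalized treatment selection". The section on remaining evidence gaps gives the reason: "since we do not yet know for whom ICBT is particularly suitable".

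The whole method is in the section Analysis of predictors and moderators, which is two sentences long. The outcome is binary: "We will analyse predictors and moderators of response and remission status at 3- and 12-month follow-up using repeated k-fold cross validation". The validation scheme is stated as "using repeated k-fold cross validation with 10 folds and 20 repeats to reduce the risk of model instability". The measure is the AUC averaged over the repeats, and its purpose is to "distinguish between responders/remitters and non-responders/non-remitters".

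The section names no model, no candidate variables, no covariate-by-treatment term, no contrast between arms and no rule for calling a variable a moderator. The only interaction in the Statistical analysis section is treatment group by time, and it contains no baseline covariate.

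**The concern.** A predictor is a baseline variable related to outcome. A moderator is a baseline variable for which the difference between arms changes with its value. Asking which patients suit internet CBT is a moderator question.

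The AUC described scores how well a model ranks patients by their chance of response or remission. A variable that forecasts outcome equally in all three arms can earn a high AUC and still say nothing about which arm to choose. If only the AUC is reported, prognostic variables could be read as grounds for choosing between guided, unguided and face-to-face treatment, and a reader would have no estimate from which to judge true moderation.

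**Working it through.** The predictor and moderator section gives no sample size, power or effect figure, so there is nothing to reproduce. The check is whether the stated measure can tell moderation from prognosis.

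**Inputs from the documents.** 120 patients, 40 per arm (Study design); binary outcome; 10 folds and 20 repeats; alpha 0.05 (Statistical analysis).

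**Assumptions, not in the documents.** One standard-normal baseline covariate; 50% response at its mean in every arm; log-odds slopes of 0.6 to 1.2 per SD; lightly penalised logistic models for the cross-validation; 100 simulated trials per scenario.

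**Step 1: algebra.** Let the model have its own intercept and slope in each arm g: logit P(response) = a_g + b_g·x. Take any data set and replace x by −x in the two internet arms. The maximum-likelihood fit changes only the sign of b_g in those arms, and every patient's fitted probability stays the same. The AUC therefore stays the same too. But this change turns a covariate with a common slope (no moderation) into one with opposite slopes (full reversal). For the unpenalised model the equality is exact, whatever the effect size or response rate.

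**Step 2: simulation.** Slopes are log-odds per SD. The last column is a 2-df likelihood-ratio test of arm by covariate at 0.05.

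| Slope in f2f / internet arm 1 / internet arm 2 | AUC, arm + covariate | AUC, arm × covariate | Interaction test rejects |
|---|---|---|---|
| 1.2 / 1.2 / 1.2 (no moderation) | 0.748 | 0.742 | 3% |
| 1.2 / −1.2 / −1.2 (full reversal) | 0.522 | 0.742 | 100% |
| 1.2 / −1.2 / 0 | 0.443 | 0.662 | 98% |
| 1.2 / 0.6 / 0.6 (moderate) | 0.651 | 0.645 | 23% |

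Rows 1 and 2 have the same interaction-model AUC, as Step 1 predicts; the interaction test separates them. In row 2 the gain from adding the interaction (0.742 − 0.522 = 0.220) is informative, but the plan specifies no such comparison. In row 4 there is no gain (0.645 against 0.651).

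**Step 3: what an explicit interaction can deliver.** Take a 50:50 binary moderator, response probability p and 40 per arm, so 20 per cell.

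- SE of a two-arm difference = √(2p(1−p)/40). At p = 0.5 this is 0.112.
- SE of the difference between two such differences = √(4p(1−p)/20). At p = 0.5 this is 0.224, twice as large.
- Detectable with 80% power at two-sided 0.05 (multiplier 1.960 + 0.842 = 2.802): main effect 2.802 × 0.112 = 31 percentage points; interaction 2.802 × 0.224 = 63 points.
- At p = 0.3 or 0.7 the figures are 29 and 57 points.

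The factor of two, √[(4/20)/(2/40)] = 2, also holds for a continuous outcome with a common variance.

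**The case against.** **The section names no model, so interactions are unspecified rather than excluded.** This is correct as a reading of the text, and it limits what may be claimed. A reader might infer from row 2 of the table that a strong moderator would score near chance (0.522). That holds only for a model with main effects alone, which the plan does not state. The objection does not rescue the criterion, though: with interactions in the model, the AUC is the same with no moderation and with full reversal.

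**The plan uses AUC to summarise model performance and does not say that a high AUC makes a variable a moderator.** This is also true. But no other quantity is planned, so nothing reported would bear on moderation.

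**An explicit interaction would have little power.** This stands. The test rejected in only 23% of trials in the moderate case, and the detectable difference in effect is 57 to 63 percentage points. It is a reason to report estimates with intervals and call them exploratory, not a reason to report a quantity that answers another question.

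**Response status is a legitimate clinical outcome.** Agreed. A reader might also infer a definite loss of power from using it in place of the continuous score. The documents do not support a figure: the Interventions section defines non-response by Y-BOCS reduction together with CGI-I, so response is neither a simple split of Y-BOCS nor based on Y-BOCS alone.

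**Conclusion.** The concern holds for the moderator part of objective 5. The stated criterion measures prediction of outcome and can take the same value with no moderation and with complete reversal of a covariate's effect between arms (0.742 in both simulated cases), even with interactions in the model. The equality follows from algebra; the particular AUCs and rejection rates rest on the assumed slopes, 50% response and 100 trials per scenario.

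Two wider conclusions are tempting and not supported. One is that objective 5 as a whole cannot be answered: it also covers predictors, for which repeated cross-validated AUC is a sound measure. The other is that the trial's main result is compromised: the objective is secondary and exploratory, and the non-inferiority analysis of Y-BOCS at 3 months does not depend on it.

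The change should be made, because a better analysis is available on data already being collected.

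**What to change.** 1. Keep repeated cross-validated AUC for predictors of response and remission.
2. For moderators, list the candidate baseline variables before analysis. For each, add the covariate and its interactions with group and time, including covariate by group by time, to the planned mixed model on continuous clinician-rated Y-BOCS.
3. Report the interaction at 3 months for guided ICBT against f2f and for unguided ICBT against f2f, each with its confidence interval, labelled exploratory.
4. Optionally, report alongside this the cross-validated performance for response and remission with and without the interaction terms. This stays close to the existing plan, but it can miss moderate moderation (row 4 of the table).
5. Treat any 12-month moderator result with caution. The Interventions section offers f2f CBT to internet-arm non-responders after the 3-month assessment, so later status in those arms may reflect a second treatment.

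The cost is a few sentences in the plan, a short list of variables and a few extra model fits. The downside is wide interaction intervals at 40 per arm, which should be reported as such.

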### **Limitations**

There are several potential threats to the validity and generalizability of the current trial results, some of which apply to most clinical trials. First, the trial was designed to maximise the chances of the results being as generalizable as possible. However, despite the best of our efforts to recruit both clinic- and self-referred individuals, it will be difficult to confidently claim that our participants will be representative of the entire population of OCD patients in Sweden. For example, we will not know if our results are generalizable to patients with comorbid autism spectrum disorder or to patients who are too ill to seek help and participate in clinical studies. Second, it is impossible to conduct double-blinded clinical trials of behavioural interventions. In an effort to increase transparency, our design includes careful checks of the extent to which raters are blind to the group allocation. Third, while our study is well powered to test the non-inferiority hypothesis, it may not be powered to test the same hypothesis for all secondary measures or for the cost-effectiveness calculations. Fourth, patients in the unguided ICBT arm still have contact with health care professionals at baseline, during treatment and after treatment (e.g., bi-weekly telephone assessments, post-treatment and follow-up appointments). An entirely unguided treatment would involve limited or no contact with health care professionals.

### **Patient and public involvement**

We received input from patients from three previous OCD internet CBT trials which guided the design of the current study. In the current trial, no patients were involved in the design of the study or in the decision of outcome measures. Neither will patients be involved in the recruitment of participants or in the decision of the research question. A patient organization for OCD and related disorders (the Swedish OCD Foundation) will be involved in the recruitment of participants by informing their members about the study. We will assess the burden of the trial interventions on the patients by collecting information about adverse events, quality of life, and time spent on the treatment. We will gather information about the patients satisfaction with treatment through an online self-rating questionnaire at the end of treatment. We plan to disseminate the results of the research to study participants and to the Swedish OCD Foundation.

## ETHICS AND DISSEMINATION

The trial will be conducted in compliance with this study protocol, the Declaration of Helsinki and Good Clinical Practice (GCP). Karolinska Trial Alliance (KTA) is an external party that will monitor the study every 6 months and ensure that the study follows GCP, i.e. that all participants give informed written consent and that study related materials are handled correctly. All professionals involved in the study will attend a course in GCP and get certified by the KTA.

The study has been approved by the Regional Ethics Board of Stockholm (REPN 2015/1099-31/2) and registered at Clinicaltrials.gov (NCT02541968), and will be reported in accordance with the CONSORT statement for non-pharmacological trials.(52) Ethical risks are deemed minimal and both f2f CBT and ICBT have well-documented efficacy.

### Current trial status

Recruitment of participants started in September 2015 and the last participant is expected to reach the primary end-point (3-month follow-up) in February 2019. Primary data analysis will begin in April 2019. The naturalistic follow-up phase of the trial will continue until November 2019.

## CONCLUSION

OCD is associated with significant suffering, loss of function across multiple life domains, high suicide risk, and large societal costs. ICBT has great potential to increase access to evidence-based care for a large group of sufferers that normally do not receive evidence-based psychological treatments. The study outlined in this protocol is the first direct comparison of ICBT and gold standard f2f CBT and is a crucial step before ICBT can be recommended for use within the regular health-care system. The study will provide new insights into the effectiveness of different treatment modalities for OCD and the health economic evaluation will help decision-makers to rationally allocate available resources. Implementation of ICBT in regular healthcare would dramatically increase the availability of effective treatment to those suffering from OCD.

### Competing interests

All authors declare: no support from any organization for the submitted work; no financial relationships with any organizations that might have an interest in the submitted work in the previous three years; no other relationships or activities that could appear to have influenced the submitted work.

## Funding

This study is funded by the Swedish Research Council (K2013-61P-22168) and the regional agreement on medical training and clinical research (ALF) between Stockholm County Council and Karolinska Institutet.

## FIGURE CAPTIONS

Figure 1. CONSORT-flow diagram

# Interim power analysis to KTA

(Source interim-power-analysis-to-kta.pdf)

## Real data

What to do:

1. Remove the hashes (#) in the code block below to make the code run as intended.
2. Select the attached CSV-file called **ICBTvsF2F\_powercalc\_data.csv**.
3. Run the code.
4. Report corresponding numbers from the output: variance of id, variance of time, residual variance.

```
# df_realdata <- read.csv(file.choose())  
# fit_real <- lmer(total ~ (1 | id) + (1 | time), data = df_realdata) # summary(fit_real)
```

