### **Sample size calculation**

In order to provide accurate estimates for the power calculation in the current trial, we will use individual-level data from a previous study of therapist-guided ICBT with identical Y-BOCS assessments by blinded raters and six repeated observations.(14) To calculate the required sample size, we used a bootstrap simulation with 1000 samples using the following assumptions, based on data from the previous trial: a variance of the random intercept of 10.5, a variance for the random slope of 0.04, and a within- individual residual variance of 20.4. With 3 treatment groups and 8 observations (Y-BOCS) per patient, we estimated that a total of 120 participants would be needed to detect a slope difference between two groups (i.e. group 1 vs. group 2 and group 1 vs. group 3) of 3 points at 3-month follow-up with over 90% power. We will request an interim power analysis by the Karolinska Trial Alliance to test these assumptions, using data from 80 individuals, and adjust sample size if power is lower than anticipated (see supplementary file 1 for a detailed description).

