## Results

- id has a variance of **12.77** (Random intercept)
- time has a variance of **10.02** (Random slope)
- The residual variance is **14.10** (Within-individual residual variance)

624     **Statistikakademin AB** [name] [contact] www.statistikakademin.se

625     [name] [name]

626

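### The interim code has no patient-level slope, so the 10.02 reported as a random-slope variance is between-visit spread and does not test the planned 0.04

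*Combined protocol and SAP*

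**What the plan says.** The Sample size calculation section gives three variance components taken from an earlier trial: "a variance of the random intercept of 10.5", "a variance for the random slope of 0.04" and a "within- individual residual variance of 20.4". No time unit accompanies the 0.04. With eight Y-BOCS observations per patient and 120 participants, the section claims power above 90% for a 3-point slope difference at the 3-month follow-up. It then says: "We will request an interim power analysis by the Karolinska Trial Alliance to test these assumptions, using data from 80 individuals", with the sample size to be adjusted if power turns out lower.

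The Statistical analysis section specifies a model with a random intercept and a random slope for each individual, plus fixed effects of time, group and their interaction.

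The supplement (Interim power analysis to KTA, Real data) fits "fit_real <- lmer(total ~ (1 | id) + (1 | time), data = df_realdata". Its Results list reads "id has a variance of 12.77 (Random intercept", "time has a variance of 10.02 (Random slope" and "The residual variance is 14.10 (Within-individual residual variance". The supplement as shown gives no recomputed power and no sample-size decision.

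**The concern.** In lmer syntax, `(1 | time)` treats visit as a grouping factor and gives each visit its own random intercept. A patient-level slope would be written `(time | id)` or `(1 + time | id)`, and no such term is in the code. There is no fixed effect of time either, so the average improvement over treatment goes into the variance attached to `time`. That variance is then reported under the name of a different parameter.

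Slope variance strongly affects power for a slope difference. If the interim step is to confirm or change the sample size, it must estimate that quantity. The code shown has no parameter that corresponds to it.

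**Working it through.** **Inputs from the documents.** Planning variances 10.5, 0.04 and 20.4; eight observations; 3 points; power above 90% (Sample size calculation). 40 per arm (Study design). Upper limit of a 90% interval, so one-sided 5% (Statistical analysis). Interim outputs 12.77, 10.02 and 14.10 (supplement, Results).

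**Assumptions, not in the documents.** Zero intercept–slope covariance, no dropout, complete visits, and the 3-point difference reached at the last of the eight visits. Time is coded either as visit index 0–7 or as weeks 0, 2, …, 12, 15.

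**1. The planning figure.** Let v0, v1 and ve be the intercept, slope and residual variances. With Z = [1, t] and V = Z·diag(v0, v1)·Zᵀ + ve·I, generalised least squares gives the standard error (SE) of the slope difference. Multiplied by the length of follow-up, it gives the SE of the difference at the last visit. Power = Φ(3/SE − 1.645).

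- Visit index, common baseline: SE = 0.957, so Φ(3.13 − 1.645) = 0.93. This agrees with the plan. At two-sided 5% it is 0.88.
- Visit index, separate baselines: SE = 7·√[2(0.04 + 20.4/42)/40] = 1.135, so power is 0.84.
- Weeks 0–15, common baseline: 0.83.

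One ordinary coding reproduces the claim. The planning figure is therefore not shown to be wrong, but it depends on the unstated time unit.

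**2. What the interim model estimates.** For balanced data, REML for this call equals the two-way ANOVA estimators, with var_time = (MS_time − MS_res)/n_id. If patients truly have slopes with variance v1, T is the number of visits, t̄ the mean visit time and S²t the sample variance of the visit times, the expected outputs are:

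- time = sample variance of the visit means (v1 cancels)
- residual = ve + v1·S²t
- id = v0 + v1·(t̄² − S²t/T)

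For visit index, S²t = 6 and t̄² − S²t/T = 12.25 − 0.75 = 11.5.

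A simulation with 80 patients, eight visits, v0 = 10.5 and ve = 20.4 confirms this:

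| True slope variance | time variance, 9-point linear fall | time variance, no mean change |
|---|---|---|
| 0 | 9.94 | about 0 |
| 0.04 | 9.92 | about 0 |
| 0.2 | 9.91 | about 0 |
| 0.5 | 9.93 | about 0 |
| 1.0 | 10.03 | about 0 |

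The output follows the average improvement and does not respond to the slope variance.

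**3. What 10.02 stands for.** For a linear fall, the implied drop is 7·√(10.02/6) = 9.05 points by visit index, or 15·√(10.02/26.125) = 9.29 points in weeks to week 15. If the fall is linear to week 28 over nine visits, it is about 10.5. Other trajectory shapes give somewhat different values.

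**4. Consistency check.** A true slope variance of 10.02 would force the interim residual to at least 6 × 10.02 = 60.1 (visit index) or 26.125 × 10.02 = 261.8 (weeks). The reported residual is 14.10, so the label conflicts with the supplement's own output.

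**5. What the interim outputs allow.** Solve ve = 14.10 − 6·v1 and v0 = 12.77 − 11.5·v1 (visit index). The id variance limits v1 to 12.77/11.5 = 1.11. The residual alone would allow 14.10/6 = 2.35. One-sided power with a common baseline is:

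| v1 | v0 | ve | Power |
|---|---|---|---|
| 0 | 12.77 | 14.10 | 0.98 |
| 0.04 | 12.31 | 13.86 | 0.97 |
| 0.2 | 10.47 | 12.90 | 0.90 |
| 0.4 | 8.17 | 11.70 | 0.79 |
| 1.0 | 1.27 | 8.10 | 0.57 |
| 1.1 | 0.12 | 7.50 | 0.55 |

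With weeks 0–15 the limit is about 0.27, and power is 0.98 at v1 = 0, 0.90 at 0.04 and 0.59 at 0.2. At the planning intercept and residual variances with visit-index time, power drops below 90% once v1 exceeds about 0.095, and below 80% above about 0.26.

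**The case against.** The strongest reply is that the interim output still carries information. The visit term absorbs the visit means, so leaving out a fixed time effect does little harm to the other two components. Omitted slope heterogeneity can only add to the residual, so 14.10 is roughly an upper estimate of it and lies below the planned 20.4. The outputs also put a ceiling on the slope variance. This stands, but the ceiling still leaves power anywhere between about 0.55 and 0.98, which neither confirms the assumption nor triggers a change.

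A second reply is that the supplement is short and the step that would feed its numbers into a power calculation is not displayed. This also stands. The supportable statement is that the code shown does not test the slope assumption, not that nobody ever tested it.

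Third, the error leaves the primary analysis model, the margin and the confidence interval untouched, and achieved precision will show in the interval. That is true and limits the consequence to the sample-size check.

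Two stronger readings are tempting. A reader might set 10.02 against 0.04, infer a 250-fold rise in slope variance and conclude that power has collapsed. The two numbers measure different things, 14.10 is incompatible with such a slope variance, and the supplement itself makes no such comparison. A reader might also take 0.04 as per week squared, run time out to week 28 over nine visits, and obtain power of about 59% with the interim residual. That choice drives the result: the same formula gives 54% for the protocol's own planning values, where the plan claims over 90%. The documents state neither that unit nor nine observations.

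**Conclusion.** The point holds. The interim code lacks a patient-level slope, 10.02 is mislabelled, and the slope assumption that the interim analysis was meant to test is not tested by the code shown. That much follows from the model syntax and needs no assumption about the data. The 12.77 and 14.10 are affected too, because both absorb slope heterogeneity.

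Underpowering is not shown. The range of about 0.55 to 0.98 assumes visit-index time, eight observations, a common baseline, zero intercept–slope covariance and no dropout. It shifts with the time unit, which the plan does not give. The true slope variance cannot be recovered from the published numbers because the interim data are not in the documents.

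**What to change.** 1. Establish and state the time scale on which 0.04 was estimated.
2. Refit the same data with a patient-level slope on that scale, for example `total ~ factor(time) + (1 + time_num | id)`, where `time_num` is time in the planning unit. If the check stays pooled over arms, note that any between-arm difference in slope inflates the slope variance. Otherwise add group and group-by-time terms, as in the Statistical analysis section.
3. Report the intercept variance, slope variance, their covariance, the residual variance and the time unit.
4. Re-run the power simulation with these values, and base the power statement and any sample-size decision on that output.
5. Withdraw the random-slope label from the 10.02.

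The cost is one refit on data already held, one simulation run and a corrected supplement. The restated power may be less favourable. Current trial status expects the last participant to reach the primary endpoint in February 2019, so room to act on the result may be limited. The record should be corrected in any case.
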